**Fig 2 pone.0330915.g002:**
[figure not shown]
Panel A – 4D ultrasound scan at 34 weeks gestation; Panel B – 1-month-old infant wearing fNIRS headgear, supported by a researcher while sleeping in the home setup; Panel C – 1-month-old infant wearing EEG headgear supported by a researcher while sleeping in the home setup; and Panel D – and 5-month-old infant wearing fNIRS headgear at the research lab visit.

### Neuroimaging measures

*Functional Near Infrared Spectroscopy (fNIRS)* uses near-infrared light to monitor changes in concentration and oxygenation of haemoglobin in the brain that occur as a result of changes in neural activity. This imaging technique consists of a soft cap where NIR light sources and detectors are mounted and provides several advantages for its use with infant populations such as being silent, relatively portable, and not requiring rigid head stabilization. This allows for use in home and naturalistic settings, improving infants’ and families’ compliance with the study.

In the PIPKIN study, we use a wearable High-Density Diffuse Optical Tomography (HD-DOT) fNIRS system, which uses dense arrays of sources and detectors at multiple separations and with overlapping measurements, allowing for the reconstruction of three-dimensional images with depth information. The HD-DOT system LUMO (Gowerlabs Ltd, UK) consists of multiple independent tiles, each of which is equipped with 3 dual-wavelength LED sources (at 735, 850 nm) and 4 photodiode detectors [50–52]. These tiles can be flexibly clipped into an infant-friendly soft cap to acquire measurements of different brain regions. Our cap for newborn and 1-month-old infants is made from flexible elastane material and features a Velcro chin strap (Easycap GmbH, Germany). It includes 12 tiles positioned over the frontal and temporal regions, providing 36 source locations, 48 detector locations, and a total of 1728 channels per wavelength (Fig 2). For 5-month-old infants, the cap is made of neoprene and includes 15 tiles, offering 45 source locations, 60 detector locations, and a total of 2700 channels per wavelength, covering analogous regions (Fig 2). The sampling frequency of the device is 12.5 Hz.

fNIRS tasks are completed in the home around the first and second week of life and at one month, and then repeated at five months when families are invited to the Cambridge Babylab. The fNIRS paradigms assess a range of cognitive functions and domains, namely social cognition [53], habituation and novelty detection [54] and functional connectivity.

*fNIRS Social/Non-social:* This task consists of dynamic social and non-social videos that are presented consecutively, but not synchronized with auditory social and non-social stimuli. Social videos show a life-size female face moving her eyes and playing games such as peek-a-boo, while non-social videos show a moving toy. Between each condition, as baseline, infants are presented with non-social static images such as cars and trucks. To accommodate infants’ varying awareness states, three variations of this task have been implemented: i) For newborn and 1-month-old infants in awake state, dynamic social videos and dynamic non-social videos are presented with no auditory stimuli [4]. ii) For newborn and 1-month-old infants during sleep, only social and non-social auditory stimuli are presented. Social auditory stimuli include sounds of laughing and crying, while non-social auditory stimuli include sounds of running water, bells or squeaky toys. iii) infants at 5 months perform the full task awake where visual social stimuli are presented alongside auditory stimuli so that a third of the trials contain social auditory stimuli, a third non-social auditory stimuli, and the remaining third are silent ([53], for details of the full task see [55]). Task version i) was discontinued after 97 testing sessions (0–7 day sessions = 28, 7–14 day sessions = 34, 1-month sessions = 35) due to difficulties in acquiring sufficient data from participants. A significant proportion of infants failed to remain awake for the duration of the task, and among those who did, the proportion of infants providing good-quality data was low. The primary challenges included infants becoming fussy and the presence of substantial motion artifacts in the recorded signals, both of which impeded the collection of reliable data. For the remaining testing sessions newborn and 1-month-old infants were tested while asleep according to version ii) above.

*fNIRS Habituation and Novelty Detection* [54]: In this task, infants are presented with the same sentence of around 8 seconds produced by a female voice, repeated fifteen times (i.e., habituation). The next five trials consist of the same sentence, this time produced by a male voice (i.e., novelty). In the last five trials the initial condition (i.e., female voice) is repeated again five times. At newborn visits (including 1-month visit) the infants are asleep, at the 5-month visit an experimenter quietly manipulates toys to keep the infant entertained and in a calm, alert state.

*fNIRS Functional connectivity:* Two tasks are conducted to assess functional connectivity. In newborns and 1-month-old infants, spontaneous task-free hemodynamic activity is recorded during natural sleep for around 20 minutes (to obtain a total of around 10 minutes of motion-free data by combining clean segments, each lasting at least 100 seconds). To improve compliance with the task, infants at 5 months are presented with alternating social (i.e., nursery rhymes) and non-social (i.e., dynamic toys) videos with auditory content of two minutes duration each. Each of these blocks is presented between two and three times.

Where newborn or 1-month-old infants are viewing videos or completing tasks while sleeping in the home, the infant is held in a comfortable position by the experimenter, and the 13-inch screen is placed approximately 30 cm from their face, either attached to a stand, or held in position by a second experimenter (visual angle = 57 degrees). At 5 months, while at the Babylab, all infants are awake for all tasks and for visual tasks are sat on a parent’s lap, 60 cm from a 24-inch presentation screen (visual angle = 54 degrees). Infant behaviour at both sessions is recorded using a webcam attached to the stimuli presentation screen.

The full fNIRS battery, while infants sleep, lasts around 40 minutes for recordings in the home and while awake at 5 months, around 30 minutes at lab visits.

*Electroencephalography (EEG)* is a non-invasive neuroimaging technique that records the electrical activity of the brain and offers high temporal resolution so that rapid electrophysiological changes occurring within a millisecond time-frame can be captured. In the PIPKIN study, EEG is recorded using the 20 channel Neurolectrics Enobio gel-based portable EEG system with passive electrodes with a sampling rate of 500 Hz (Fig 2). The reference and ground electrodes are placed unilaterally on infants’ left mastoid.

*EEG Auditory Oddball:* This task assesses habituation and novelty detection at 1 and 5 months, using the protocol described in Katus et al, [56]. Infants are presented with 15 minutes of auditory stimuli consisting of repeated sounds in randomised order: 80% are frequent sounds (500 Hz pure tones), 10% infrequent sounds (white noise) and 10% trial unique sounds (range of sounds). At all timepoints this task is done while the infant is sleeping. The Auditory Oddball task allows us to examine event-related neural responses to repeated and novel sounds, and to build Bayesian models of the neural computations underlying novelty responses.

*EEG Resting State*: Spontaneous task-free EEG is recorded for around 10 minutes during natural sleep.

*EEG Gaze ERP task:* This visual task completed at 5 months assesses neural sensitivity to eye gaze. For each trial the infant sees a colour image of a female face against a white background on the screen, with the female’s gaze directed either towards or away from the infant. The face then displays gaze shifts, alternating between looking towards and away from the infant. In one third of trials, infants see ‘visual noise’ stimuli which are constructed from the same faces presented in gaze trials, but with phase spectra randomised. For more details of the protocol see Elsabbagh et al [57].

The full EEG battery lasts around 25 minutes for recordings in the home (Fig 2) and about 40 minutes at lab visits.

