### Neuroimaging measures

The fNIRS and EEG data will be pre-processed and analysed to identify statistically significant regions of brain activation, from which markers of brain function in relation to specific tasks will be extracted. The resulting data will be used to generate measures of brain function for age. Multivariate data analyses will enable the exploitation of longitudinal and cross-sectional variation in testing-age to fit growth curve models. These are valuable for providing a framework for efficient age-adjusted comparisons of differences in average trajectories according to socio-economic status, groupwise differences in variability, and also for characterizing the range of individual developmental trajectories.

*fNIRS functional connectivity:* The analysis of fNIRS functional connectivity data will involve different methods to describe functional brain networks and their developmental trajectory. One such method is the seed-based correlation approach (e.g., [91]), which involves selecting a region of interest as a seed and computing the correlation coefficient between the seed and all other brain regions. Another approach will use group-level independent component analysis with dual regression to compute spatially independent patterns of brain activity (e.g., [51, 92]). This method generates a set of group-level maximally independent spatial maps (i.e., functional networks) that can be regressed out to the subject level using spatiotemporal or dual regression to obtain subject-specific spatial maps [93]. These individual-level maps can be used to assess individual trajectories of functional connectivity development.

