*EEG resting state:* For the resting-state EEG analysis, data collected at 1 and 5 months will be used to examine functional connectivity and frontal alpha asymmetry (FAA). Functional connectivity will be measured using common methods, such as coherence, phase-locking value (PLV), or weighted phase lag index (wPLI). The maturation of connectivity patterns will be assessed between 1 and 5 months. Frontal alpha asymmetry will be analysed by comparing log transformed power in the left and right frontal areas, which may indicate early tendencies toward approach or avoidance behaviours. Stability of membership in the relative left or right frontal asymmetry groups will be assessed between 1 and 5 months.

In summary, neuroimaging data will be analysed via multiple approaches to investigate the development and variability of ERP responses and functional brain networks across the early stages of life, with the goal of identifying associations with specific and general environment factors.

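### The EEG connectivity indices named for the 1-to-5-month comparison depend on the amount of clean data, so unequal yield could look like maturation; for fNIRS, unequal duration affects precision only

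*Protocol article*

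**What the plan says.** **EEG.** Methods and materials, Neuroimaging measures, gives one recording length for the resting state: "Spontaneous task-free EEG is recorded for around 10 minutes during natural sleep". Table 3 places it at 1 and 5 months, asleep both times. The device is a "20 channel Neurolectrics Enobio gel-based portable EEG system", which gives 20 × 19 / 2 = 190 channel pairs. The Data analysis section then states: "Functional connectivity will be measured using common methods, such as coherence, phase-locking value (PLV), or weighted phase lag index (wPLI". Maturation is to be assessed between 1 and 5 months.

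**fNIRS.** In newborns and 1-month-olds, "spontaneous task-free hemodynamic activity is recorded during natural sleep for around 20 minutes", the aim being "to obtain a total of around 10 minutes of motion-free data by combining clean segments, each lasting at least 100 seconds". At 5 months infants watch alternating social and non-social "videos with auditory content of two minutes duration each", and "Each of these blocks is presented between two and three times". That is 2 conditions × 2 minutes × 2 or 3 = 8 to 12 minutes presented, or 4 to 6 minutes per condition. The planned metrics are seed-based correlation and group ICA with dual regression, used for individual trajectories and as predictors of individual differences.

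**Models.** The neuroimaging analysis text says growth curve models will serve for "groupwise differences in variability, and also for characterizing the range of individual developmental trajectories". The section Analyses and data availability adds full information maximum likelihood (FIML), which uses partially complete records.

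**The concern.** Coherence, PLV and wPLI are magnitudes. Estimated from a finite number of epochs they are positive even when nothing is coupled, and the excess grows as epochs become fewer. If infants yield fewer clean epochs at one age than the other, connectivity at that age can look stronger without any change in the brain. The same applies to a comparison between resource groups.

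FIML does not remove this. It deals with absent records, whereas a value computed from short data enters as fully observed. Elsewhere the article does allow for recording length: fetal movements become rates per minute, and NBAS state changes are scaled to 30 minutes. It states no counterpart for connectivity.

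The fNIRS problem is milder. A correlation from less clean signal has about the same mean but a larger sampling error. Apparent spread between infants then includes more estimation noise, and individual profiles are less reliable as predictors.

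**Working it through.** **Inputs from the article:** about 10 minutes of EEG at each age; 20 channels; about 20 minutes of sleep fNIRS with a target of about 10 clean minutes in segments of at least 100 s; 8 to 12 minutes of fNIRS blocks at 5 months; a minimum of 80 datasets per hypothesis. The 10-minute fNIRS target is a design aim with no formula behind it. It is coherent: 6 × 100 s = 600 s, half of 20 minutes.

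**Assumed, because not given:** 2-second epochs, coupling strength, clean-data yields, fNIRS bandwidth 0.07 Hz (range 0.05 to 0.10), true between-infant SD of Fisher z 0.15 (range 0.10 to 0.20).

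**1. EEG, no coupling.** For K independent epochs, E[squared coherence] = 1/K and E[PLV] = √(π/(4K)). At K = 300, √(0.7854/300) = 0.051; at K = 150, √(0.7854/150) = 0.072. Simulation agrees:

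| Clean data (K) | Squared coherence | PLV | wPLI |
|---|---|---|---|
| 600 s (300) | 0.003 | 0.051 | 0.065 |
| 300 s (150) | 0.007 | 0.072 | 0.092 |
| 120 s (60) | 0.017 | 0.114 | 0.145 |
| 60 s (30) | 0.033 | 0.163 | 0.208 |

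**2. EEG, moderate coupling.** At coupling 0.3, from 600 to 120 s, coherence goes from 0.093 to 0.104 and PLV from 0.242 to 0.257, while wPLI stays flat (0.413 to 0.410). At coupling 0.5, from 600 to 60 s, wPLI falls slightly (0.660 to 0.643).

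**3. False change, single pair.** Paired t-test, 80 infants, coupling 0.3, no true change, 400 runs:

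| Clean data at the two ages | Coherence | PLV | wPLI | Pairwise phase consistency |
|---|---|---|---|---|
| 600 v 600 s | 4.5% | 4.5% | 6.2% | 4.5% |
| 600 v 300 s | 7% | 7% | 4.8% | 5% |
| 600 v 120 s | 36% | 32% | 4.5% | 5.8% |

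**4. False change, mean of 190 weakly coupled pairs.** 80 infants, identical true coupling at both ages, 12 runs per setting. At 600 v 300 s the false rise was 0.003 for coherence, 0.015 for PLV and 0.016 for wPLI, significant in all 12 runs. The between-infant SD at 600 s was 0.018 for PLV and 0.031 for wPLI, so the shift is about 0.015/0.018 = 0.8 SD and 0.016/0.031 = 0.5 SD. At 600 v 480 s all 12 runs were again significant; at 600 v 600 s none were.

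A second simulation with other settings (mean coherence 0.1, SD 0.03, 30 runs) compared 240 with 120 epochs. PLV rose from 0.094 to 0.110 and wPLI from 0.141 to 0.158, with false significance in about 90 to 100% of runs, against about 7% for debiased squared wPLI. At 240 v 200 epochs the PLV rate was about 20%.

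**5. fNIRS precision.** Effective n = 2 × bandwidth × time; SE(z) = 1/√(n − 3); reliability = 0.15² / (0.15² + SE²).

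| Clean time | Effective n | SE(z) | Reliability |
|---|---|---|---|
| 600 s | 84 | 0.11 | 0.65 |
| 300 s | 42 | 0.16 | 0.47 |
| 100 s | 14 | 0.30 | 0.20 |

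At 100 s, SE(z) ranges from 0.24 (0.10 Hz) to 0.38 (0.05 Hz). If one group of 40 had 10 clean minutes and another had 5, the variance ratio would be (0.0225 + 0.0256)/(0.0225 + 0.0123) = 1.38. An F-test of equal variances would then be falsely significant about 17% of the time.

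**The case against.** **The article is condensed.** Inclusion thresholds, epoch rules and estimator variants commonly sit in a fuller plan. The index list is introduced as examples, so a debiased variant is not excluded. This stands: the lack of a minimum clean duration is no fault in itself. What remains is that every index the article does name is length-sensitive, at least under weak coupling, and these are attached to an age contrast.

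**A reader might infer that connectivity is computed from whatever clean data each infant happens to yield.** The article does not say so. It sets a target and a segment minimum for sleep fNIRS; it states no matching rule. That target also concerns fNIRS, whereas the upward bias belongs to the EEG indices.

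**Nothing shows that EEG yield differs by age.** Both recordings are about 10 minutes of natural sleep. This stands too. For fNIRS a difference is more plausible, since connectivity is recorded asleep up to 1 month and awake at 5 months, and the article reports fussiness and motion artefact in an awake newborn task.

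**The high false-positive rates depend on the settings.** They need weak coupling averaged over many pairs, and they give each infant identical true coupling at both ages. With an assumed SD of true change of 0.05, a PLV shift of 0.016 in 80 infants gives 0.016/(0.05/√80) = 2.9 standard errors, detected about 80% of the time; with SD 0.10, about 30%. The gap between about 20% and 12 of 12 runs at mild imbalance makes the same point.

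**The sentence on variability follows text about task-related markers.** It may not be meant for connectivity. The fNIRS connectivity paragraph does speak of individual trajectories, so the precision point holds for that use.

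**Conclusion.** The point holds as a foreseeable and avoidable weakness in the named EEG indices. Coherence and PLV, and wPLI when coupling is weak, rise as clean epochs fall. An imbalance in yield between ages or groups could therefore account for part of an apparent change. Its size ranges from nearly nothing (a single pair at coupling 0.3, 600 v 300 s) to about 0.8 between-infant SD for PLV (mean of 190 weakly coupled pairs, same imbalance). Which applies here cannot be known, because no yields are given.

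Three stronger readings are not supported. The documents do not show that recording quality would be reported as maturation, only that it could be. wPLI does not always rise; at moderate coupling it is flat or slightly lower. Unequal fNIRS duration does not bias mean trajectories; it lowers reliability (0.65 at 10 minutes to 0.47 at 5, under the assumptions above) and adds noise to apparent individual differences.

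**What to change.** **EEG:** name a debiased index (pairwise phase consistency or debiased squared wPLI) for the 1-to-5-month contrast, or draw the same number of clean epochs from every infant at both ages. In the single-pair check pairwise phase consistency stayed near nominal throughout. Debiased squared wPLI drifted down somewhat at very short durations: 0.170 at 600 s to 0.152 at 60 s for coupling 0.3. A sensible minimum epoch count therefore still helps.

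**fNIRS:** before interpreting individual trajectories or variability, enter each Fisher z with its sampling variance, using an effective sample size that allows for autocorrelation, or compute connectivity on an equal clean duration per recording.

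**Reporting:** give clean minutes by age and by resource group for both modalities.

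**Cost:** analysis wording and code only; no change to data collection. The rule can be fixed before results are analysed. Matching epochs or durations discards some clean data; debiasing or weighting avoids that loss.

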### Behavioural/Neurocognitive measures

*The Neonatal Behavioural Assessment Scale (NBAS)* is a structured clinical assessment of infant neurology and behaviour, which can be performed from the first few days of life and involves observation of: the infant in both asleep and awake states, responses to stimuli (while asleep), and behaviours relating to social interaction (while awake) such as tracking a moving face, and motor skills and reflexes. It is regarded as the most comprehensive examination of newborn behaviour and requires an initial training period culminating in assessment and certification as described in *The Neonatal Behavioural Assessment Scale* Manual [58]. In PIPKIN, the NBAS is performed during the first two weeks of life, and again at 1 month. The assessment usually takes around 20 minutes, depending on how the infant responds to the assessment and any time needed to calm the infant down.

During the PIPKIN study we amended the NBAS to suit the wider research paradigms being carried out, in order to ensure research sessions were not too taxing for younger infants. In particular, some of the stimuli often used to elicit responses and help babies transition from sleep to awake states, such as reflex items, were removed given infants underwent neuroimaging and other experiences that could elicit such responses. Moreover, certain items were measured and recorded across the whole research session, such as state changes and regulation, with the length of the session documented alongside this so that the number of state changes per 30 minutes (the length of a typical NBAS) could be calculated after the session.

*The Mullen Scales of Early Learning (MSEL)* is a standardised assessment battery that measures cognitive ability and motor development across five domains: gross motor, fine motor, visual reception, expressive language, and receptive language. The MSEL assessment is carried out at the 5-month lab visit, using the standardized protocol appropriate for the age of the infant, as detailed in the Mullen Scales of Early Learning Manual and the Item Administration Book [59].

*Parent-child interaction videos (PCI)* are recorded at 1 and 5 months. The parent is asked to engage in natural play with their child while three video cameras record the interaction; one trained primarily on the infant, one on the parent, and a side view that captures both. At 1 month, a 5-minute play session without toys is recorded in the home with the parent sitting sideways on a sofa (leaning against the arm, their feet up on the seat), with the infant propped up on their knees so they are face-to-face. This position was chosen as a sofa is a constant across varying home environments. At 5 months, a 10-minute recording is made during the lab visit; 5 minutes with no toys, and 5 minutes playing with a standardised set of toys. The parent is seated or kneeling on the floor opposite the infant lying on an angled mat so that they are face-to-face. Where fathers/partners are available during the visit, PCI recordings are made with both parents. Offline PCI videos are later coded to assess multiple aspects of parent and child behaviour, and engagement between the two. Parental interaction style has been shown to associate with child neural and cognitive development [32,60,61].

*Eye-tracking tasks* are carried out at the 5-month lab visit, using the Tobii Pro TX300 remote eye-tracker. The infant sits on the parent’s lap, approximately 40 cm from the 24-inch screen. Following a short calibration sequence, the infant completes four tasks which are interleaved into a single battery which takes around 15 minutes. As some tasks are gaze contingent, the duration of the battery depends somewhat on the infant’s performance.

The eye-tracking battery includes: the *Gap/Overlap task* [62,63] which measures the infant’s ability to disengage from a fixated stimulus, with maturation of the visual system leading to shorter disengagement latencies [64,65]; the *Non-social Contingency task* which examines infant’s sensitivity to contingency and predictability; the *Fifty faces task* (a 40 second long naturalistic video of people going about everyday life, and looking at the camera) and the *Dancing Ladies task* [66] where infants view faces embedded in naturalistic and semi-naturalistic scenes, allowing investigation of visual exploration and face preference as well as standard measures of individual differences such as fixation durations and saccadic reaction time measurements.

